### Analytical method

#### Primary endpoints

The change in MADRS total scores from weeks 0 to 4 during the acute treatment period will be analyzed using MMRM, in which the MADRS total score at week 0 as well as the interaction between the total score at week 0 and time point as continuous covariates (fixed effects), and the intervention, age, diagnosis, institution, time point, and interaction between the intervention and time point as categorical variables (fixed effects), and the response variables included will be the change in MADRS total scores measured at weeks 2 and 4. An unstructured covariance model will be fitted to intra-individual covariance structure, and Kenward–Roger degrees-of-freedom (DF) method will be applied to estimate the DF. The hypothesis test will be performed based on the least square estimates. Main comparison between the interventions will be performed by contrast at 4 weeks. As sensitivity analyses, analysis of covariance (ANCOVA) after LOFC, after BOCF for missing data at 4 weeks, and complete case ANCOVA will be performed. As secondary analyses, the change in the MADRS total score from weeks 0 to 4 will be analyzed using Wilcoxon rank-sum test. Interim analysis will not be performed.

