### Number of participants

Number of participants who obtained consent: active stimulation group, 48; sham stimulation group, 48; total, 96 (1:1 randomization).

Number of participants analyzed: active stimulation group, 38; sham stimulation group, 38; total, 76 (1:1 randomization).

A meta-analysis performed by McGirr et al. included patients with a depressive episode of bipolar disorder, and the effect size in the amount of change in depressive symptoms was 0.48 for low-frequency stimulation to the right prefrontal cortex (9). Since there were no previous studies on concomitant pharmacotherapy in bipolar disorder, the effect size was estimated as 0.65 based on the results of the aforementioned meta-analysis. The sample size was estimated assuming the effect size of 0.65, two-sided alpha equal 0.05, and power of 0.80. Overall, 80% of participants will be considered appropriate to be included in the double-blind study according to the inclusion and exclusion criteria. Therefore, with the sample size multiplied by 1/(1–0.20), the number of participants who will need to provide consent is 48 for each group; thus, we will need to recruit 96 participants.

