### Randomization, allocation concealment

Cases will be enrolled and assigned to each stimulation group by the staff in charge of assignment in a centralized and aggregated manner. The subjects will be assigned with stratified block randomization. The stratified factors are sex and age (20–50, 51–75 years). Magventure will prepare the assignment table (corresponding table) on which six-digit patient codes are filled in, and the staff in charge of assignment will assign subjects to the actual or sham stimulation groups based on the assignment table. The staff in charge of assignment and the staff supporting the personal information management will not be allowed to recruit subjects, obtain IC, or perform intervention or neuropsychological testing.

The specific procedure is as below:

The staff in charge of recruiting study subjects and obtaining their informed consent (IC) will perform necessary assessment on the candidate patients according to the inclusion and exclusion criteria, after obtaining their written consent.The case enrollment form on which prescribed information are filled in will be sent to the staff in charge of assignment to apply for enrollment and assignment.After confirming the condition of the study subjects, the staff in charge of assignment will fill in the case enrollment number and six-digit patient code on the enrollment confirmation based on the assignment table prepared in advance and send it back to the study staff in each medical institution.The study staff in each medical institution will receive the enrollment confirmation, which contains the case enrollment number and patient code, from the staff in charge of assignment.

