#### Secondary endpoints

For patients in whom remission is noted at week 4 during the acute treatment period, the days to relapse/recurrence from week 0 during the observation period will be analyzed using the Kaplan–Meier method and log-rank test.

Cox proportional hazards regression analysis will be performed, in which the MADRS total score at week 0, intervention, diagnosis, age, and institution will be explanatory variables.

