#### Other endpoints

The response and remission rates at week 4 in the acute treatment period and at week 28 in the subsequent observation period will be analyzed using logistic regression analysis, in which the MADRS total score at week 0, intervention, diagnosis, age, and institution will be explanatory variables. As a secondary analysis, Fisher test will be used. For MADRS, HAMD-17, PHQ-9, CGI, YMRS, EQ-5D, BACS, and THINC-it, a comparison between the active and sham stimulation groups will be performed using Wilcoxon rank-sum test at week 4 during the acute treatment period and at week 28 in the subsequent observation period, respectively.

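### Sex is a randomisation stratification factor but is left out of the primary MMRM and the logistic models; if sex is prognostic, some precision is forgone

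*Protocol article*

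**What the plan says.** Under Randomization, allocation concealment: "The subjects will be assigned with stratified block randomization", and then "The stratified factors are sex and age (20–50, 51–75 years".

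Under Analytical method, Primary endpoints, the terms of the MMRM are listed in full. The continuous covariates are week-0 MADRS and its interaction with time point. The categorical fixed effects are "the intervention, age, diagnosis, institution, time point, and interaction between the intervention and time point as categorical variables (fixed effects". The covariance structure and the degrees-of-freedom method are fixed as well. ANCOVA after LOCF, ANCOVA after BOCF and complete-case ANCOVA follow as sensitivity analyses, without a covariate list of their own.

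Under Other endpoints, response and remission at weeks 4 and 28 are analysed by "logistic regression analysis, in which the MADRS total score at week 0, intervention, diagnosis, age, and institution will be explanatory variables". Under Analytical method, Secondary endpoints, the Cox model has the same covariates.

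Sex appears in none of these lists. Age, the other stratification factor, appears in all of them. So do diagnosis and institution, which are not stratification factors.

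**The concern.** Stratified blocks keep the arms nearly balanced on sex, so sex contributes little to the true sampling variability of the treatment difference. A model that omits sex still counts any sex-related variation as residual. If sex predicts the outcome, the reported standard error then exceeds the true one: confidence intervals are too wide, the type I error falls below its nominal level, and part of the precision gained by stratifying is not used.

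The covariate lists also do not match the design, since one of the two stratification factors is carried into the analysis and the other is dropped without explanation. Because the primary model is specified so closely, an analysis plan that followed it would leave sex out.

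**Working it through.** **1. The plan's own figure.** The inputs, from Number of participants, are: "The sample size was estimated assuming the effect size of 0.65, two-sided alpha equal 0.05, and power of 0.80".

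- n per arm = 2 × ((1.960 + 0.842)/0.65)² = 37.15, rounded up to 38.
- 38/(1 − 0.20) = 47.5, rounded up to 48 consented per arm.
- Power at 38 per arm is 0.809 by the normal formula and 0.799 by the t calculation.

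Both stated figures reproduce. Neither depends on whether sex is in the model.

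**2. Size of the effect by formula.** The documents give no relation between sex and MADRS change, so a range is assumed. Hold the total SD at 1, assume a 50:50 sex split, and let b be the sex difference in SD units.

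- Share of variance due to sex: R² = b²/4. Any other split gives a smaller share for the same b.
- Ratio of the model standard error without sex to that with sex: 1/√(1 − R²).
- Power with sex in the model: Φ(0.65 × √(38/2)/√(1 − R²) − 1.960).

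For b = 0.5, R² = 0.0625, the ratio is 1/√0.9375 = 1.033, and power is Φ(2.833/0.968 − 1.960) = 0.833, against 0.809 without sex.

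**3. Check by simulation.** There were 10,000 trials of 76 patients per scenario, with blocks of 4 within sex-by-age strata. The block size and the even splits by sex and age are assumptions. The analysis was a week-4 ANCOVA with baseline, age stratum, diagnosis and institution, with and without sex. It stands in for the week-4 MMRM contrast with complete data. Covariates other than sex had no effect on the simulated outcome, so b is the sex difference remaining after them.

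| b (SD) | R² | SE ratio | Formula power with sex (0.809 without) | Simulated type I error, without / with sex | Simulated power, without / with sex |
|---|---|---|---|---|---|
| 0 | 0 | 1.000 | 0.809 | 0.047 / 0.048 | 0.773 / 0.776 |
| 0.2 | 0.010 | 1.005 | 0.813 | 0.048 / 0.049 | 0.778 / 0.782 |
| 0.3 | 0.0225 | 1.011 | 0.818 | 0.048 / 0.050 | 0.782 / 0.789 |
| 0.5 | 0.0625 | 1.033 | 0.833 | 0.042 / 0.052 | 0.782 / 0.799 |
| 0.8 | 0.160 | 1.091 | 0.871 | 0.036 / 0.052 | 0.794 / 0.842 |

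The Monte Carlo standard error of a 5% rejection rate is √(0.05 × 0.95/10,000) = 0.0022. The drops to 0.042 and 0.036 are therefore real, and the 0.052 values are compatible with 5%.

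The mechanism shows directly in the null runs. Without sex, the mean model standard error against the actual SD of the estimate is 0.235 against 0.236 at b = 0, 0.235 against 0.229 at b = 0.5, and 0.236 against 0.219 at b = 0.8.

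Simulated power at b = 0 is below the formula value because the simulated model carries covariates that do nothing in these data and the arms can be slightly unequal. The comparison that matters is the one within each row.

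**4. What was not computed.** No figures were produced for the logistic or Cox models.

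**The case against.** The strongest reply is that the harm is conditional and probably small. A reader might infer from the omission that the primary test is in fact conservative and that power is in fact lost. The documents do not support that, because they report no sex effect. At b = 0 nothing is lost, and at 0.2–0.3 SD the loss is under 1 point. The largest loss in the table needs a sex difference of 0.8 SD, which exceeds the treatment effect of 0.65 that the trial itself assumes. This objection stands, and it limits the point to a conditional statement.

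A reader might also infer that the trial falls short of its planned power because of the omission. It does not. With total SD held fixed, simulated power without sex is never below its value at b = 0 (0.773). What is lost is a gain that the stratified design makes available. The absence of an allowance for dropout in the sample size is a separate matter and adds nothing here.

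A third tempting step is to apply the argument to the time-to-relapse analysis. The protocol describes the Kaplan–Meier and log-rank analysis for patients in remission at week 4. That subset is formed after randomisation, so balance on sex is not assured. Events may also be few. As an illustration, the response rates cited in the Introduction (44.3% and 25.3%) give 38 × 0.443 + 38 × 0.253 = 26.4 responders, and the remission cut-off is stricter than the response definition. If diagnosis and age each have two levels, the Cox model already has about six parameters: baseline score, intervention, diagnosis, age and two for the three institutions. A further term is not free there. This objection also stands.

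The reply that the matter can be left to an analysis plan is weaker, because the protocol already lists the covariates of the primary model.

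**Conclusion.** The point holds as a modest issue of efficiency and consistency. The mismatch between stratification factors and model terms is certain; its consequence is not. If sex is related to MADRS change after the other covariates, the primary test is conservative: about 2 power points and a type I error near 4.2% at 0.5 SD, and about 5 points (6 by formula) and near 3.6% at an extreme 0.8 SD. Below about 0.3 SD the loss is under 1 point, and with no sex effect it is nil.

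The treatment estimate is not biased, type I error is not inflated, and no stated sample-size figure changes. These sizes rest on an even sex split, blocks of 4, complete week-4 data and an ANCOVA in place of the MMRM. For the logistic models the case is one of consistency only.

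**What to change.** Under Analytical method, Primary endpoints, add sex as a categorical fixed effect to the MMRM, in the same way as age, and carry it into the LOCF, BOCF and complete-case ANCOVAs. State that age enters in the randomisation groups (20–50, 51–75). The model already treats age as categorical, and these are the only age groups in the document, so this merely makes the link explicit. Under Other endpoints, add sex to the logistic models for consistency. For the Cox model, adding sex is optional and should be weighed against the number of events.

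The cost to the primary model is one degree of freedom. Sex is already recorded (Evaluation), and the simulation shows no material penalty if sex is irrelevant (power 0.776 with sex, 0.773 without). Recruitment is expected to run to February 2027, no interim analysis is planned, and unblinding for analysis follows data fixation. The amendment can therefore be made blind, whereas adding sex after unblinding would look post hoc.

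### Seven secondary scales, and MADRS at week 28, are compared as scores only by a Wilcoxon test without baseline as a covariate; adjusting for baseline could gain 0 to about 14 points of power

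*Protocol article*

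**What the plan says.** **Primary endpoint (Analytical method, Primary endpoints).** The main analysis is an MMRM on MADRS change that includes "the MADRS total score at week 0 as well as the interaction between the total score at week 0 and time point as continuous covariates", plus age, diagnosis and institution, with the contrast at week 4. The sensitivity analyses are three ANCOVAs: after LOCF, "after BOCF for missing data at 4 weeks, and complete case ANCOVA will be performed". Separately, as secondary analyses, "the change in the MADRS total score from weeks 0 to 4 will be analyzed using Wilcoxon rank-sum test".

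**Scales (Analytical method, Other endpoints).** The plan states: "a comparison between the active and sham stimulation groups will be performed using Wilcoxon rank-sum test". This is to be done at weeks 4 and 28 for eight scales: HAMD-17, YMRS, CGI, PHQ-9, BACS, THINC-it, EQ-5D and MADRS. No covariate is named.

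**Other between-arm models.** The Cox model for relapse or recurrence and the logistic models for response and remission both adjust for week-0 MADRS, diagnosis, age and institution. Fisher's test is only secondary to the logistic models.

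**Status of the scales.** Changes in these scales are listed secondary endpoints under Outcomes.

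**The concern.** Change from baseline usually correlates with the baseline value. Where it does, the part of the variation in change that baseline explains stays in an unadjusted test as noise. A rank test with baseline as a covariate removes that noise and still does not rely on normal scores.

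The protocol adjusts for week-0 severity in its regression models but not here. The matter is of little weight for MADRS at week 4, which the MMRM and ANCOVAs already cover. It weighs more for the seven other scales and for MADRS at week 28, where the Wilcoxon test is the only between-arm comparison of scores that the protocol states. Any loss there falls directly on a reported secondary result.

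**Working it through.** **Inputs.** From Number of participants: "The sample size was estimated assuming the effect size of 0.65, two-sided alpha equal 0.05, and power of 0.80", with 38 analysed per arm and 48 consenting per arm. The SDs at weeks 0 and 4 (s0, s1) and their correlation (ρ) are not in the protocol, so they are assumed over a range.

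**1. The plan's own figure.** n per arm = 2(1.960 + 0.842)² / 0.65² = 2 × 7.85 / 0.4225 = 37.2, so 38. Then 38 / (1 − 0.20) = 47.5, so 48. Both figures reproduce. A t-test at 38 per arm has power 0.799.

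**2. What sets the gain.** Var(change) = s0² + s1² − 2ρ·s0·s1. The variance left after baseline adjustment is s1²(1 − ρ²). With equal SDs the ratio of the two is 2/(1 + ρ), for example 2/1.5 = 1.33 at ρ = 0.5. With s0 = 0.6·s1 and ρ = 0.6 it is 0.64/0.64 = 1.00: change is then uncorrelated with baseline and adjustment gains nothing.

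**3. Simulation.** 38 per arm, effect 0.65 SD of change, bivariate normal scores, 3,000 trials per setting. The Monte Carlo standard error is √(0.77 × 0.23 / 3000), about 0.8 points. The rank ANCOVA regresses ranked change on arm, ranked baseline and indicators for the four sex-by-age strata. The strata have no effect on the outcome in these settings.

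| s0/s1 | ρ | Variance ratio | Wilcoxon on change, % | Rank ANCOVA, % | Gain, points |
|---|---|---|---|---|---|
| 1 | 0.3 | 1.54 | 76.6 | 90.4 | 13.8 |
| 1 | 0.5 | 1.33 | 78.4 | 86.6 | 8.2 |
| 1 | 0.7 | 1.18 | 77.7 | 83.3 | 5.6 |
| 1 | 0.8 | 1.11 | 77.4 | 80.8 | 3.4 |
| 0.6 | 0.2 | 1.17 | 77.2 | 82.0 | 4.8 |
| 0.6 | 0.4 | 1.05 | 77.5 | 79.3 | 1.8 |
| 0.6 | 0.6 | 1.00 | 77.3 | 77.0 | −0.3 |

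With no true effect (equal SDs, ρ = 0.5), the rejection rate was 5.0% for Wilcoxon and 5.4% for rank ANCOVA. The gain is not bought with false positives.

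**4. Second parameterisation, baseline only, no strata.** With baseline SD 5–7, residual SD 7–8 and slope of week 4 on baseline 0.3–0.8 (all assumed), power was 76–78% for Wilcoxon on change and 78–90% for rank ANCOVA. At an effect of 0.48, the meta-analytic value cited under Number of participants, it was 51–52% against 53–66%.

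**5. Strata.** The randomisation section states: "The stratified factors are sex and age (20–50, 51–75 years". A Wilcoxon test stratified on these four cells (van Elteren), without baseline, had 75–78% power. With an assumed effect of 0.3 SD per factor it had 77.6%, against 77.7% unstratified. The gain therefore comes from baseline.

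**6. Score or change.** Other endpoints does not say whether scores or changes are ranked, while Outcomes lists changes. If week-4 scores were ranked without adjustment, power at slope 0.8 would fall to roughly 58–70%, against 77–79% for rank ANCOVA. At slope 0.3 the two are close (82–89% against 83–90%). Baseline adjustment therefore performs well under either reading.

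**The case against.** The strongest reply is that nothing here is wrong. The Wilcoxon test holds its type I error, contradicts no other passage, and sits beside an adjusted MMRM and three adjusted ANCOVAs. That stands, and it limits the point to efficiency.

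A reader might infer more than the protocol supports:

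- *That the test ignores baseline.* It does not when applied to change, which subtracts the week-0 score. Only the covariate is missing.
- *That power is certainly lost.* The table shows no gain when change is uncorrelated with baseline. The HAMD-17 entry threshold of 18 may narrow the baseline spread. With s0 at 0.6 of s1 the gain is only 0 to 5 points.
- *That leaving out the sex and age strata costs power.* Step 5 shows no measurable cost.
- *That the MADRS Wilcoxon is there to confirm the MMRM without normality, so that disagreement would cast doubt on the primary result.* The protocol gives it no such purpose and lists it apart from the sensitivity analyses.
- *That Wilcoxon is the only comparison for all eight scales.* MADRS at week 4 has the MMRM and ANCOVAs. HAMD-17 also enters through response and remission, which have adjusted logistic models.

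It is also fair that the simulation uses one generic normal outcome at 38 per arm. Nothing was computed specifically for PHQ-9, CGI, YMRS, EQ-5D, BACS, THINC-it or week 28. The direction carries over to any scale whose change correlates with its baseline; the exact figures do not.

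**Conclusion.** The point holds as a minor efficiency improvement to a stated method. For HAMD-17, PHQ-9, CGI, YMRS, EQ-5D, BACS and THINC-it, and for MADRS at week 28, the only stated between-arm test of the scores leaves out baseline as a covariate, unlike the protocol's regression models. At 38 per arm and an effect of 0.65, the cost is between nothing and about 14 points of power. It rests on assumed SDs and an assumed correlation or slope, with normal scores. In no setting tried was the adjusted rank test materially worse. The MADRS Wilcoxon under Primary endpoints is the weaker part of the point, because it drives neither the primary conclusion nor the sample size.

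**What to change.** **Other endpoints.** Make a baseline-adjusted comparison the main between-arm test at weeks 4 and 28: for example, rank ANCOVA of change on that scale's own week-0 score, wherever one is collected. Say explicitly that change is analysed, in line with Outcomes. Keep the plain Wilcoxon as supportive if wished.

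**Primary endpoints.** Replace the secondary Wilcoxon test with rank ANCOVA on week-0 MADRS, or add the latter beside it. Stratifying by sex and age need not be added for power.

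**Cost.** No new data or visits. The test is named in the protocol, so the wording change goes through the route under Protocol amendments (review board and Ministry). Rank ANCOVA is also less easily paired with a simple shift estimate than Wilcoxon. Recruitment is expected to run to February 2027 and no interim analysis is planned, so the change can be made before unblinding.

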#### Secondary endpoints

For patients in whom remission is noted at week 4 during the acute treatment period, the days to relapse/recurrence from week 0 during the observation period will be analyzed using the Kaplan–Meier method and log-rank test.

Cox proportional hazards regression analysis will be performed, in which the MADRS total score at week 0, intervention, diagnosis, age, and institution will be explanatory variables.

#### Other endpoints

The response and remission rates at week 4 in the acute treatment period and at week 28 in the subsequent observation period will be analyzed using logistic regression analysis, in which the MADRS total score at week 0, intervention, diagnosis, age, and institution will be explanatory variables. As a secondary analysis, Fisher test will be used. For MADRS, HAMD-17, PHQ-9, CGI, YMRS, EQ-5D, BACS, and THINC-it, a comparison between the active and sham stimulation groups will be performed using Wilcoxon rank-sum test at week 4 during the acute treatment period and at week 28 in the subsequent observation period, respectively.

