### Inclusion criteria

Patients will be included if they meet the following criteria:

Patients who meet the diagnostic criteria of bipolar disorder including types I and II with depressive episodes according to the *Diagnostic and Statistical Manual of Mental Disorders 5th Edition* (12) (DSM-5). However, in the case of a rapid cycler or mixed episode, the patient will be excluded from the study.Patients aged 20 years or older and 75 years and younger at the time of consent.Patients with a total 17-item Hamilton’s Rating Scale for Depression (HAMD-17) (13) score ≥18.Patients who have had a depressive episode within the last 3 years.During the current depressive episode, patients who have not responded to any of the following pharmacotherapies for more than 8 weeks without antidepressants (4).

 - Lithium, ≥0.8 mEq/L blood concentration - Quetiapine, 300 mg/day - Olanzapine, 5–20 mg/day - Lurasidone, 20–60 mg/day - Lamotrigine, 200 mg/day

The reason for setting each inclusion criterion is discussed below.

The reason for the use of HAMD-17 as an inclusion criterion is that a previous study conducted by O’reardon et al. (14). and other studies on magnetic stimulation employed HAMD-17 as an inclusion criterion and evaluated the efficacy with MADRS as the primary endpoint. The pilot study of refractory bipolar disorder conducted by Kito et al. also used HAMD-17 as an inclusion criterion and MADRS for the main efficacy evaluation. Thus, the reason for using HAMD-17 as an inclusion criterion is to be consistent with the large exploratory study of rTMS (conducted by O’reardon et al.), thereby enabling comparison. The reason for using MADRS instead of HAMD-17 for efficacy evaluation is that HAMD-17 has more parameters to evaluate sleep and allocates higher scores to the conditions than MADRS does. Therefore, similar to these evaluations, this study has also been designed to use HAMD-17 as an inclusion criterion and MADRS as the primary endpoint. Furthermore, we selected a total score of 18 or more in HAMD-17 because this was used as an inclusion criterion in the study of O’reardon et al. and because this study examines moderate or more severe bipolar disorders.

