### Definition of terms

The terms of the endpoints of this study are defined as follows:

Response: A response will be defined as a decrease of ≥50% in the HAMD-17 score measured at week 0 during the acute treatment period or a total HAMD-17 score of ≤12.Remission: The presence of remission will be defined as a total HAMD-17 score of ≤7.Relapse/recurrence: When a participant experiences conditions that meet the diagnostic criteria for depressive, manic, or hypomanic episodes defined in the DSM-5 after remission, during the acute treatment period, such conditions will be defined as relapse/recurrence. Additionally, relapse will be defined as disease exacerbation within half a year of remission, and recurrence will be defined as disease exacerbation after more than half a year of remission.

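### The logistic models for HAMD-17 response and remission adjust for baseline MADRS and omit baseline HAMD-17: a small, avoidable loss of precision

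*Protocol article*

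**What the plan says.** Protocol article, Definition of terms: "A response will be defined as a decrease of ≥50% in the HAMD-17 score measured at week 0" during acute treatment, "or a total HAMD-17 score of ≤12". For remission: "The presence of remission will be defined as a total HAMD-17 score of ≤7". Neither definition uses MADRS.

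Protocol article, Analytical method, Other endpoints: "The response and remission rates at week 4 in the acute treatment period and at week 28 in the subsequent observation period" are analysed by logistic regression, in which "the MADRS total score at week 0, intervention, diagnosis, age, and institution will be explanatory variables". An unadjusted companion follows: "As a secondary analysis, Fisher test will be used".

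Two other places bear on the point. The primary analysis (Analytical method, Primary endpoints) adjusts MADRS change for week-0 MADRS, that is, on the same scale. The Inclusion criteria section sets the HAMD-17 entry floor ("we selected a total score of 18 or more in HAMD-17") and explains that HAMD-17 gives sleep more weight than MADRS does. The protocol therefore does not itself treat the two scales as interchangeable.

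**The concern.** Where an outcome is derived from a scale, the baseline value on that scale is usually its strongest available predictor. Here a related but different scale is used instead, and the value on the outcome's own scale, already needed to compute response, is left out. Randomisation is stratified by sex and age only (Randomization, allocation concealment), so baseline severity is not balanced by design. With 38 analysed patients per arm, a chance difference in baseline HAMD-17 would be only partly taken up by baseline MADRS.

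At stake is the precision of two results that clinicians will read closely and that the trial was not sized for. The covariate list is stated explicitly, so this is not a detail left open for an analysis plan.

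**Working it through.** **1. The plan's own figure.** The sample size rests on MADRS change, "assuming the effect size of 0.65, two-sided alpha equal 0.05, and power of 0.80". Per arm: 2 × (1.960 + 0.842)² / 0.65² = 15.70 / 0.4225 = 37.2, rounded up to 38. Consent target: 38 / (1 − 0.20) = 47.5, rounded up to 48. Both match the protocol, and neither depends on the covariate in question.

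**2. What baseline HAMD-17 does to the cut-offs.** The two limbs of the response definition give a week-4 cut-off of max(12, H/2), where H is week-0 HAMD-17. Remission requires 7 or less whatever H is.

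| H | Response cut-off | Fall needed for response | Fall needed for remission |
|---|---|---|---|
| 18 | 12 | 33.3% | 61.1% |
| 20 | 12 | 40.0% | 65.0% |
| 24 | 12 | 50.0% | 70.8% |
| 26 | 13 | 50.0% | 73.1% |
| 30 | 15 | 50.0% | 76.7% |
| 36 | 18 | 50.0% | 80.6% |

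Baseline moves the response cut-off only above 24, and never moves the remission cut-off. If baseline HAMD-17 were normal with mean 21 and SD 4.5 before truncation at 18 (an assumption), the share at 18 to 24, with half-point continuity limits, would be 0.563 / 0.782 = 72%. For most patients, then, baseline acts as a prognostic factor: a higher start means a longer way to a fixed target.

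**3. How well MADRS stands in.** The documents give no correlation between the scales. If it is 0.80 before selection, truncation at 18 lowers it to about 0.66 to 0.73. Baseline MADRS would then explain 0.66² = 44% to 0.73² = 53% of the variance in baseline HAMD-17.

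**4. Power when only the baseline score is exchanged.** All rates, SDs and correlations below are assumptions.

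*Set A*: 76 patients, 1,500 runs per setting, shift 0.65 SD, sham response about 39%, sham remission about 12%. The model holds intervention and one baseline score. Entries are power with MADRS → power with HAMD-17.

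| Correlation of the two baselines | Correlation of baseline with week-4 HAMD-17 | Response | Remission |
|---|---|---|---|
| 0.4 | 0.2 | 0.602 → 0.605 | 0.462 → 0.475 |
| 0.4 | 0.4 | 0.627 → 0.646 | 0.464 → 0.490 |
| 0.4 | 0.6 | 0.658 → 0.723 | 0.494 → 0.561 |
| 0.6 | 0.2 | 0.622 → 0.619 | 0.460 → 0.467 |
| 0.6 | 0.4 | 0.637 → 0.662 | 0.472 → 0.498 |
| 0.6 | 0.6 | 0.672 → 0.735 | 0.520 → 0.587 |
| 0.8 | 0.2 | 0.603 → 0.601 | 0.463 → 0.460 |
| 0.8 | 0.4 | 0.648 → 0.657 | 0.489 → 0.501 |
| 0.8 | 0.6 | 0.689 → 0.728 | 0.548 → 0.584 |

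In the six settings with baseline to week-4 correlation 0.2 or 0.4, the change runs from −0.3 to +2.6 points. In the three at 0.6 it runs from +3.6 to +6.7.

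*Set B*: 3,000 runs per setting, with diagnosis, age group and a three-level institution also in the model; slope of week-4 on baseline HAMD-17 of 0.6 or 0.9. Response went from 61.1% to 62.3–63.1%; remission from 34.0% to 34.8%, or from 37.7% to 40.9%.

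*Set C*: correlation of the baselines 0.80 before truncation (0.70 after). With a HAMD-17 slope of 0.6 and no separate MADRS effect, response was 56.1% with MADRS and 56.0% with HAMD-17; remission 47.0% and 49.0%. With a HAMD-17 slope of 0.3 plus a MADRS slope of 0.25, response was 59.0% and 57.6%; remission 50.1% and 49.4%. In the last case MADRS was marginally the better covariate.

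**5. No treatment effect.** In 2,000 null runs, rejection with MADRS and HAMD-17 was 5.4% and 5.3% for response, and 4.0% and 3.8% for remission. In the null setting of Set A the mean response log odds ratios were 0.042 and 0.045, with rejection 6.9% and 6.3% (6.1% with no covariate). The slight excess is thus not specific to the MADRS model.

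**The case against.** The strongest defence is that nothing here is invalid. Treatment is randomised, and a model adjusted for any prespecified baseline covariate is a legitimate comparison. Week-0 MADRS also serves as the single severity covariate in the MMRM, the Cox model and the logistic models, which is a defensible convention, and the protocol explains why it prefers MADRS for judging efficacy. These are low-tier endpoints with an unadjusted test alongside. Entry at 18 or more weakens the link between the scales, but it also narrows the spread of baseline HAMD-17 and so limits any chance imbalance. Finally, a simulation in which week-4 HAMD-17 depends only on baseline HAMD-17 favours that covariate by construction.

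Most of this stands, and it limits the point to precision. It does not explain the choice: the stated preference for MADRS concerns the primary outcome, not the covariate for outcomes defined on HAMD-17.

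Two stronger readings should be resisted. A reader might infer that baseline HAMD-17 fixes the score every patient must reach. It does not for remission, nor for response at baselines of 18 to 24. A reader might also take the 2–7% smaller log odds ratio of the MADRS model in Set B as bias. Odds ratios are non-collapsible, so a less prognostic covariate yields a conditional odds ratio nearer to 1 without the estimate being wrong.

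**Conclusion.** The mismatch of scales is real and unexplained, and its consequence is minor. The likely cost is roughly 0 to 3 points of power in most assumed settings, up to about 7 where baseline HAMD-17 strongly predicts week-4 HAMD-17. There is no cost, or a slight advantage for the present plan, where baseline MADRS carries its own prognostic information. The documents give none of the correlations, SDs or event rates behind these figures, so the size is indicative only; the simulations also treat a single follow-up time.

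The documents do not support any claim that the primary MADRS analysis, the sample size or the type I error is compromised. This is a free improvement of low impact.

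**What to change.** Under Other endpoints, in the logistic models for response and remission, use the week-0 HAMD-17 total in place of the week-0 MADRS total. Keep baseline MADRS for MADRS outcomes. If MADRS is retained, give the reason in a sentence.

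Replace rather than add. At the assumed remission rates of about 12% and 30%, 38 × 0.12 + 38 × 0.30 gives about 16 remissions. Taking diagnosis and age as two-level and institution as three-level, the model already has six terms besides the intercept (intervention 1, diagnosis 1, age 1, institution 2, baseline 1), or about 2.7 remissions per term. A second, collinear severity score would strain it further.

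The change is one phrase and needs no new data and no extra parameter. A protocol change needs the approvals listed under Protocol amendments, so it could travel with the next amendment. The protocol describes recruitment as ongoing and unblinding as following data fixation, so it can be made blind.
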